### Blinding

Because of the nature of the interventions, neither clients, distributors nor data collectors, will be blinded to the allocation status. However, analyses will be conducted on data with identification arm allocation removed, and the trial statisticians (MN, KF, BH) will be un-blinded only after data have been finalized.

### Data managem**e**nt

Quantitative data will be captured using electronic devices (tablets). In Malawi, program data will be extracted onto optical character recognition forms and processed into a dedicated database. Incoming electronic data will be checked regularly for errors, with supplemental training provided to field staff if required. All quantitative data will be cleaned and analysed using Stata 14 or 15 [19]. All participants will be assigned a study ID number. Their names will not be linked except through paper-based recruitment logs, which will be stored in locked cupboards. Similarly, in Zambia, quantitative client-level program data will be captured using electronic devices by CBDAs onto a platform based on Open Data Kit (ODK), an open source platform that allows for data collection through the use of mobile devices in real time and offline. From the CBDA, data will be uploaded to a central computer at SFH Head Quarters via the internet on a weekly basis, and data will be password-protected to ensure confidentiality. No client names will be collected, with linkage of client data instead using barcoded unique identifiers.

Qualitative data will be recorded in two forms – observational notes and digital audio recordings – and cross-referenced for accuracy. The audio file will be transcribed verbatim, and then will then be translated into English. All data will then be transferred to and coded using a qualitative data analysis software package, such as NVivo 10 [20].

As described elsewhere [21], data on costs will be extracted from project, PSI, and Ministry of Health records of expenditure including transport and training, unit costs, and salaries. Time and motion studies will be used to estimate the proportion of time spent on HTS by staff with multiple duties. Patient direct and indirect costs incurred to access HIV testing will be identified by interview at baseline, and for HIVST by interview at endline, surveys. Anonymized data will be made available in a public repository after the project is completed and findings disseminated.

### Fidelity of intervention and process evaluation

Quantitative monitoring and evaluation will be used together with qualitative process evaluation data to assess the following questions:***Have HIVST kits been distributed in communities, and to whom?*** This will be assessed quantitatively using monitoring and evaluation data collected by CBDAs, as well as information provided by clients on the self-completed questionnaire returned with the used test kit. This will be used to assess the volume of distribution in different areas and demographics of recipients, and whether these characteristics changed over time.***Have people in the intervention communities received and used HIVST kits?*** This will be assessed quantitatively using the self-completed questionnaire returned with the used test kit and the endline household survey by asking whether households were visited by CBDAs and received HIVST kits. These data will examine whether the intervention reached the expected population. Households in both intervention and SOC arms will be asked about CBDA visits to assess contamination.***Do potential test users know how to receive care or prevention services?*** This will be assessed within the household survey at baseline and endline, and will be important for understanding whether clients could link to additional care following testing.***Would test users recommend self-testing to their family or friends?*** This will be assessed within the endline household survey, and will be used to understand whether self-testing was a generally positive experience.

A qualitative process evaluation will also be conducted for each impact evaluation, following up on the issues described above. Qualitative research related to the trial is discussed in greater detail below.

### Reporting of social harms and adverse events

While HIV testing programs are well-established in these settings, concerns remain about the possibility of HIVST leading to harmful reactions from self-testers, their partners, or their families. We will assess social harms (including all forms of gender-based violence, any physical injury or related hospitalization and death due to assault) related to the self-testing intervention using a community reporting system established in each study cluster. Adverse events (AE) and serious adverse events (SAE) will be monitored for both trials.

In Malawi, social harm and AEs disclosed by clients to CBDAs will be recorded and followed up by PSI staff and local researchers. Active community-based reporting systems, with members pre-identified through social mapping, will also be established in the evaluation villages to report social harms. In Zambia, social harm and AEs will be tracked within a reporting system including CBDAs, local health clinics, community leaders and CBDA supervisors. CBDAs will be asked to follow up with clients experiencing serious events related to HIVST as well as any action taken. AEs will be categorized by severity, with SAEs including death, hospitalization, or violent assault within 30 days of a reactive HIV self-test. SAEs will be reported immediately to the principal investigator, while other AEs will be logged and reported regularly to the study team and technical advisory group (TAG).

In addition, we will use questions within the household survey on recent testing experiences to assess whether any HIV tests were coerced, whether clients regretted testing at the time of the test or at the time of the survey. These questions will be asked for all recent HIV tests, including both HIVST and standard HTS. We will also ask women participating in the survey about experiences with IPV at baseline and endline. Finally, we will assess the prevalence of perceived HIV-related stigma in the community at baseline and endline, to assess whether these beliefs change as a result of the intervention.

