### Intervention and standard of care

Both trials will assess the effectiveness of community-distributed HIVST on HIV testing uptake using OraQuick HIV Self Tests (Bethlehem, PA USA, assembled in Thailand) including instructions-for-use translated by the manufacturer into local languages (Chichewa in Malawi; and Nyanja, Tonga, and Bemba in Zambia). The specificity and sensitivity of the test kit in a general rural population in sub-Saharan Africa will be assessed in separate studies [16]. HIVST kits will be stored and distributed by Population Services International (PSI)-Malawi or Society for Family Health (SFH)-Zambia. In both trials, CBDAs will be trained by PSI or SFH in how to explain the written self-test instructions, demonstrate correct use, and show examples of reactive and non-reactive tests to assist in reading results. Distributors will also be trained on appropriate test kit storage and information concerning linkage to confirmatory testing and ART for clients with reactive HIVST results or prevention for clients with non-reactive results. Clients will be offered the choice of testing with CBDA assistance or in private. CBDAs will also be trained in how to pre-empt, respond to and report social harm, including suicide, gender-based violence, or coerced testing. Individuals are eligible for HIVST if they are ages 16 years or older.

In Malawi, CBDAs will provide door-to-door community-based distribution of HIVST kits as well as access from their own homes, building on a pre-existing initiative providing reproductive health products. CBDAs will provide all clients who wish to test with: (1) information on the test and a demonstration on how to open and use the HIVST kit; (2) an envelope and short anonymous questionnaire to be completed by the client and returned with the kit; and (3) a self-referral form to facilitate linkage into HIV care and prevention services. CBDAs will distribute one test per resident who is interested in testing. CBDAs will visit clients after distributing the kit to enquire whether the kit has been used, collect the sealed questionnaire and used kit, and provide advice on referral to additional care if the client discloses a reactive HIVST result. Clients will also be able to drop used kits in locked boxes within each community, or return them to CBDAs at their homes.

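### The only worded SAE criterion depends on a reactive self-test, so a serious HIVST-related event after a non-reactive test or a refused kit is not named as an SAE

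*Protocol article*

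**What the plan says.** Protocol article, *Reporting of social harms and adverse events*:

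- AEs are graded by severity, "with SAEs including death, hospitalization, or violent assault within 30 days of a reactive HIV self-test". The article gives no other SAE criterion.
- The grade decides the route: "SAEs will be reported immediately to the principal investigator, while other AEs will be logged and reported regularly to the study team" and the technical advisory group (TAG).
- Social harms form a wider stream, "including all forms of gender-based violence, any physical injury or related hospitalization and death due to assault". They are to be assessed when "related to the self-testing intervention using a community reporting system established in each study cluster". No test result is required.
- In Zambia, distributors (CBDAs) follow up clients who have serious events linked to self-testing, again whatever the result.

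*Intervention and standard of care*:

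- CBDAs are trained to "report social harm, including suicide, gender-based violence, or coerced testing". No result condition is attached.
- Clients may test privately. In Malawi the questionnaire comes back sealed and anonymous, and the CBDA will "provide advice on referral to additional care if the client discloses a reactive HIVST result".

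**The concern.** The sentence announces a grading by severity and then uses a test result as part of the grade. Several harms that the protocol names can occur whatever the result: coerced testing, gender-based violence over being tested, and reactions from partners or families. Two people with the same injury from the same cause could be graded differently because one self-test line appeared and another did not, or because no test was done at all.

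The grade matters because SAE notification is the only route that the article describes as immediate. *Trial management* sets up no separate data safety monitoring board and has the TAG meet twice a year. *Interim analysis and stopping rules* sets no stopping rule. A report of few SAEs could also be read as few serious harms, when it counts only those that met a result-dependent trigger.

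**Working it through.** The plan gives no figure to reproduce. The check is a reading of the sentence, then an illustration of scale.

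**Step 1. Possible readings of the criterion.**

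- A: the 30-day reactive-test clause qualifies death, hospitalisation and assault.
- B: the clause qualifies only violent assault.
- C: as A, but the word *including* leaves the list open.

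**Step 2. Events related to HIVST set against each reading.**

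| Event | A | B | C |
|---|---|---|---|
| Assault within 30 days of a reactive test | SAE | SAE | SAE |
| Same, result not disclosed | SAE, but reporter may not know | as A | as A |
| Same, test was coerced | SAE | SAE | SAE |
| Assault after a non-reactive test | not an SAE | not named | not named |
| Assault after refusing a kit | not an SAE | not named | not named |
| Hospitalisation or suicide after a non-reactive test | not an SAE | SAE | not named |

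On every reading, assault after a non-reactive test or a refused kit is not a named SAE. Reading B rescues death and hospitalisation only. It also leaves those two with no time window and no link to testing, which makes it the less natural reading. Reading C leaves the unnamed events to each reporter's judgement.

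**Step 3. Can the trigger be applied?** The reporter has to know that the result was reactive. Private testing, anonymous questionnaires and voluntary disclosure mean that the CBDA may not know. *Data management* adds that no client names are collected in Zambia. Table 4 does list barcodes that link the returned kit and its result to the distribution record, so a result may sometimes be recovered later, but that does not help an immediate report.

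**Step 4. Share of self-tests outside the trigger.** Let r be the proportion reactive. The non-reactive share is 1 − r. The article gives no r for self-tests, so proxies are used.

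- Prevalence under *Discrete choice experiments*: Malawi 8.8%, so 100 − 8.8 = 91.2%. Zambia 13%, so 100 − 13 = 87%.
- Table 1, Malawi clinics: r = Σ(tests × percent positive) / Σ(tests) over 22 clinics and 65,688 tests = 7.27%, so 100 − 7.27 = 92.7%. Clinic positivity runs from 3.4% to 14.4%, which gives 96.6% to 85.6%.

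**Step 5. What this does not show.** The share of testers is not the share of harms. If a serious harm is R times as likely after a reactive as after a non-reactive result, the two groups contribute equally when r × R = 1 − r, so R = (1 − r)/r.

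- Malawi, prevalence: 91.2/8.8 = 10.4.
- Zambia, prevalence: 87/13 = 6.7.
- Malawi, Table 1: 92.73/7.27 = 12.8 (clinic extremes 85.6/14.4 = 5.9 and 96.6/3.4 = 28.4).

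Below these values of R, most serious harms among testers follow a non-reactive result; above them, most follow a reactive one. The article gives no R.

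**The case against.** The strongest reply is that little is lost. *Including* does not close the SAE list. The social-harm stream has no result condition and covers every study cluster. In Malawi, harms disclosed to CBDAs are recorded and followed up. The remaining AEs still reach the study team and the TAG, which also reviews social harms. The household survey asks about coercion and regret for self-tests and standard tests alike, and asks women about partner violence. The article also says that formative research will shape the harm definitions. All of this stands, and it limits the point to grading and speed. It does not remove it: an open list gives no rule for the unnamed cases, and the one rule that is worded turns on the result.

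A reader might infer more than the text supports:

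- **That events after undisclosed or coerced tests are excluded.** If the test was reactive they meet the criterion. Non-disclosure is a problem of ascertainment.
- **That the SOC arm can never have an SAE.** SOC includes no self-test distribution, so few or none are expected under this criterion. But *Fidelity of intervention and process evaluation* plans to measure contamination, and an SOC resident who obtains a kit could qualify.
- **That a comparison of arms is biased.** Table 3 lists no SAE outcome and no comparison of SAEs between arms is described.
- **That most serious harms would miss the immediate route.** Step 5 shows that this needs an assumption the documents do not supply.
- **That no test date is collected.** Table 4 is an overview, not a report form, so its silence proves nothing.

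**Conclusion.** The point holds in a limited form. The worded SAE criterion makes a grading by severity depend on a reactive self-test, at least for violent assault and on the natural reading for all three events. That is inconsistent with the result-independent harms named in the same section and under *Intervention and standard of care*. Followed as written, a serious HIVST-related event after a non-reactive test or a refused kit may take the slower route and stay out of the SAE count.

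Roughly 87% to 93% of self-tests would fall outside the named trigger, assuming that population prevalence or clinic positivity approximates self-test reactivity. The proportion of serious harms affected cannot be stated. The effect is on grading, urgency of reporting and interpretation of the SAE count; the harms themselves are still collected. This is a correction worth making, not a threat to the primary analysis.

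**What to change.** Reconcile the two sections with one event-based definition.

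1. Define an SAE by the seriousness of the event (death, including suicide; hospitalisation; violent assault) for events related to the HIVST intervention, whatever the test result and whether or not a test was done. State whether the list is complete.
2. Start the time window from a date the programme can record, such as kit offer or receipt.
3. Record test result, disclosure and relatedness as attributes of the event, not as conditions for calling it serious.
4. State how the definition applies in SOC clusters, or state that SAE counts are not to be compared between arms.
5. Align the harm lists, so that suicide and coerced testing appear wherever gender-based violence and assault do.

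The cost is a change to the definition and to the report form. The downside is that more events, some of them unrelated, will reach the immediate route and need review.

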### Trial analysis

All analyses will be completed in Stata 14, on an intention-to-treat basis, and will use methods appropriate for CRTs with a small number of clusters [18]. Reporting will conform to the 2010 CONSORT statement as applicable to cluster randomized trials [22].

Analyses will be conducted separately by country. Initial analyses will compare characteristics of households and respondents across arms at baseline. These baseline analyses will be completed before analysis of endline data begins. Characteristics of households and respondents at endline will be summarized by arm, so that imbalances can be accounted for in our final analysis. Missing data will be examined for each variable and for each cluster or individual participant. A systematic assessment of missingness will be conducted to ascertain the reason and possible mechanism for missing data by identifying the quantity of missing data and patterns within the data. Missingness will be examined by cluster and between randomised arms to assess for systematic biases.

Primary and secondary trial outcomes will be compared using cluster-level unadjusted and adjusted means of recent testing. The analysis will give each cluster equal weight. For the unadjusted analysis, the overall prevalence of the outcome for each cluster will be calculated, and a log transformation will be applied to the prevalence for each cluster if needed. If there are any clusters with no events, one event will be added to all clusters so that the log transformation can be conducted. The mean and standard deviation of the log prevalence will be used to obtain the geometric mean and associated 95% confidence intervals for each trial arm.

For the adjusted analysis, a two-stage approach will be used. First, a logistic regression model including individual-level adjustment factors but not trial arm will be fitted, and predicted probabilities from this model used to estimate the ratio of observed to expected outcome events for each cluster. This ratio will be log transformed, and a t-test of the difference between logs by arm will be used to estimate the prevalence ratio, 95% confidence interval, and *p*-value. For both unadjusted and adjusted analyses, we will report risk ratios and risk differences. If adjustment for cluster-level factors is considered necessary, this will be conducted at the second stage using linear regression of the log ratio of observed and expected values on arm and cluster level factors, with appropriate adjustment for the degrees of freedom. The adjusted analysis will serve as the primary analysis of each trial. Sensitivity analysis for the primary outcome of recent test for HIV will be carried out by comparing complete case analysis results with those where missing outcome status are re-classified as yes and no.

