### Randomization

The Malawi trial includes two stages of randomization. In the first stage, clinic catchment areas will be allocated to HIVST or standard of care arms using restricted randomization. To ensure that intervention and standard of care clinics are evenly distributed geographically across the study area, we will restrict the number of intervention clinics in each district, with larger districts to include at least 35% intervention clinics. We will balance arms in terms of number of testers, proportion of positive tests, and total catchment population across clinics. The study statistician (MN) provided a list of 1000 eligible randomization combinations to the study team and the final randomization scheme was selected in a public ceremony in Blantyre, Malawi on 21 March 2016.

In the second-stage randomization, we will randomize all CBDAs providing HIVST to home-based initiation of ART or standard of care at a 1:1 ratio. CBDAs will be randomized in blocks of varying sizes from 2 to 12 CBDAs, with the distribution of block sizes following Pascal’s triangle (i.e., 1:5:10:10:5:1).

In Zambia, clinics will be randomized 1:1 within matched pairs to receive the HIVST intervention or standard of care. Randomization was conducted by the statistician (BH) and was completed on 24 June 2016.

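### The primary analysis takes its adjustment factors from arm imbalances seen at endline, and the statement that the trial statisticians are blinded conflicts with one of them having randomised the Zambia clinics

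*Protocol article*

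**What the plan says.** Protocol article, Trial analysis: "Characteristics of households and respondents at endline will be summarized by arm, so that imbalances can be accounted for in our final analysis". The adjusted analysis has two stages. In the first, "a logistic regression model including individual-level adjustment factors but not trial arm will be fitted"; these factors are not named. Then: "If adjustment for cluster-level factors is considered necessary, this will be conducted at the second stage". On status: "The adjusted analysis will serve as the primary analysis of each trial".

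Protocol article, Blinding: "analyses will be conducted on data with identification arm allocation removed", and the three trial statisticians, listed by initials, "will be un-blinded only after data have been finalized".

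Protocol article, Randomization, on Zambia: "Randomization was conducted by the statistician". The initials given there match one of the three listed under Blinding. For Malawi, another of the three supplied 1000 candidate schemes, and the final scheme was then drawn in public.

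**The concern.** The article does more than leave a covariate list to another document. It fixes a rule: look at endline characteristics by arm, then adjust for what differs. Three consequences follow for the primary result.

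- **The model depends on the data.** Whether a factor enters turns on the observed imbalance, and for cluster-level factors on unstated judgement. The nominal 5% level assumes a model fixed in advance.
- **Post-intervention variables are not excluded.** Endline characteristics are recorded after at least 12 months of distribution. If distribution itself shifts one of them, the shift looks like an imbalance, and adjusting for it removes part of the effect.
- **The choice follows tabulation by arm.** A reader will want to know who chooses and what they know at that point. On this the article's account of blinding disagrees with its account of the Zambia randomisation.

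**Working it through.** No stated figure of the plan depends on this point, so there is none to reproduce. The check compares the sections and then illustrates the size.

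**1. What could enter the model.** Malawi's short questionnaire covers sexual behaviour (Malawi – Survey data collection). Both surveys record current ART use (Table 4), which is also a Zambia secondary outcome (Table 3). Stigma is measured expressly to see whether the intervention changes it, and women are asked about IPV (Reporting of social harms and adverse events). No sentence says that any of these will be adjusted for, and none excludes them.

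**2. Type I error under selection.** The model is the stage-2 cluster regression under no effect:

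y_j = b0 + b1·arm_j + (selected factors) + e_j,

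with b1 tested by t on n − 2 − (number of factors) degrees of freedom, two-sided 0.05. From the documents: 11 clusters per arm (Malawi). Assumed: the number of factors, their correlations and the selection threshold.

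| Rule and assumptions | Type I error |
|---|---|
| One factor fixed in advance, 11 per arm | 4.7% |
| Adjust for factors imbalanced at p<0.2; 3–5 independent factors, each correlated 0.4 with outcome | 1.5–2.9% |
| Same, factors correlated 0.3 with each other | 3.7–4.2% |
| Same rule, 3 or 5 factors, correlation with outcome 0.2 | 4.3–4.7% |
| Adjust for the single most imbalanced of 3 or 6 factors that jointly explain 40% of cluster variance, 11 per arm | 3.6–4.0% |
| Same, 6 per arm, unmatched | 3.3–3.7% |

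The lowest row is an extreme setting: independent factors with correlation 0.4 jointly explain 3 × 0.16 = 48% to 5 × 0.16 = 80% of the cluster variance. At the other end, the simulation error with 4,000 runs is √(0.05 × 0.95 / 4000) = 0.34 percentage points, so 4.3–4.7% cannot be told from 5%. The mechanism is simple. Trials with a chance imbalance are corrected, while balanced trials keep the larger unadjusted standard error and reject too seldom.

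**3. Hypothetical worst case.** If the analyst knew arm and outcome and kept the smallest p-value among the unadjusted and single-factor models, the error would be 9.2–11.1% (11 per arm, 3 or 6 factors explaining 40%), 10.3–12.4% (6 per arm) or 9.8–12.4% (3–5 factors, correlation 0.4). The article describes no such practice.

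**4. Adjusting for a post-intervention variable.** Assume a binary characteristic raised from 20% to 35% by the intervention, with odds ratio 3 for testing, analysed by the article's two-stage method with 11 + 11 clusters of 250. The prevalence ratio falls from 1.39 to 1.26. On the log scale ln 1.26 / ln 1.39 = 0.231 / 0.329 = 0.70, so about 30% of the effect is lost. The size also depends on the assumed control prevalence and direct effect. Only the direction carries over: towards no effect, when the intervention raises the characteristic and the characteristic goes with more testing.

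**5. Blinding beside randomisation.** In Zambia a person who allocated 12 named clinics is also listed as blinded until data are final. Removing the arm column does not undo that knowledge. In Malawi a listed statistician supplied candidate schemes; the article does not say that this person learned which was drawn. The third listed statistician has no recorded part in allocation. The endline data can also reveal arm: "Households in both intervention and SOC arms will be asked about CBDA visits to assess contamination". The article mentions neither recoded cluster identifiers nor an analyst outside the allocation.

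**The case against.** The strongest case on the other side has five parts.

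- **A reader might infer that the plan inflates the type I error to 10% or more.** The documents do not support this. The stated rule selects on imbalance, and that is conservative. The higher figure needs a search over p-values that no section describes.
- **A reader might infer that stigma, IPV or ART use will be adjusted for.** The text says only characteristics of households and respondents, and uses similar words for the baseline comparison. Some of these are poor candidates: IPV is asked of women only, and ART use is itself an outcome in Zambia. What stands is that nothing rules them out.
- **Measuring covariates at endline is unavoidable.** Malawi surveys different villages at endline and Zambia draws an independent sample of blocks, so endline respondents have no baseline record. This stands in full. The fault is selection on endline imbalance, not endline measurement.
- **An analysis plan that is not shown may name the factors, and baseline comparisons are finished before endline analysis begins.** Both are fair. The sentence in the article would still state a different rule and would need correcting.
- **A reader might infer that blinding fails altogether, that all three statisticians know the allocation, or that blinding was meant to protect the covariate choice.** The article documents an allocation role that reveals the arms for the Zambia statistician only. Its Blinding section does not mention covariates, endline tables could use coded arm labels, and undescribed masking of clusters could help. What stands is the contradiction for Zambia.

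**Conclusion.** The point holds as two modest, separate defects.

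First, the covariates of the primary analysis are chosen from endline imbalance by arm, with judgement over cluster-level factors and no exclusion of variables the intervention can change. The expected harm is some loss of power and possible dilution of the effect, not a raised false-positive rate. The rejection rate under no effect is about 1.5% to 4.7%. That range rests on assumed factor correlations and selection rules, and on the cluster-level stage only; the individual-level logistic stage was not simulated. The 6-per-arm run is unmatched and so does not model the Zambia pairs.

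Second, Blinding and Randomization contradict each other for the Zambia statistician. For Malawi the public draw makes blinding uncertain, but the article does not show that it was broken.

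**What to change.** 1. Delete the endline-imbalance rule. Name the covariates before endline data are opened and use them whatever imbalance appears. Limit them to variables the intervention cannot change: age group and sex (measured at endline), the baseline cluster-level proportion tested, and the design factors used for restriction or matching.
2. Keep cluster-level terms few and state them, in place of leaving them to judgement. Each costs a degree of freedom: in an unmatched comparison 22 − 2 = 20 falls to 19 in Malawi, and 12 − 2 = 10 falls to 9 in Zambia.
3. Put any further adjustment, including for an endline imbalance, in a labelled sensitivity analysis.
4. Reconcile Blinding with Randomization: state that the statistician who randomised the Zambia clinics is not blinded, and that protection comes from the locked covariate list and analysis code. For the other two, state what they know.

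The cost is wording in Trial analysis and Blinding, with no extra data: the baseline survey already records testing in the past 12 months. The downside is that a chance endline imbalance in another variable is handled only in a sensitivity analysis.
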